##### 4.5.2 Treatment Assignments

The factors defined in Section 4.5.1 will be used as stratification factors.

After the patient has been registered into the study, the values of the stratification factors will be recorded, and the patient will be assigned to one of the following treatment groups using the Pocock and Simon dynamic allocation procedure which balances the marginal distributions of the stratification factors between the treatment groups.

- 1) LCRT followed by mFOLFOX6 (or CAPOX)
- 2) LCRT followed by mFOLFIRINOX

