## 7.1 Neoadjuvant Chemoradiotherapy

**For specific questions or concerns regarding this section, please contact [name] [[contact]](mailto:[contact]) and/or [name] [[contact]](mailto:[contact]).**

Protocol treatment with long course chemoradiation therapy should be initiated within 28 days following protocol registration.

During radiation, a fluoropyrimidine must be administered concomitantly (preferred capecitabine 1650 mg/m^2/d PO in two divided doses, rounded as appropriately per institutional guidelines Monday-Friday on radiation days; Permissible Substitution: 5-Fluorouracil continuous infusion 225 mg/m^2/day, Monday-Friday on radiation days or 7 days per week based on preference of the site). If in the opinion of the investigator, a toxicity is considered to be due solely to the radiation, then the radiation can be held at the investigator's discretion. The rationale for treatment break and the duration of the break needs to be documented. Investigators are encouraged to reach out to [name] and/or [name] to discuss concerns with radiation toxicity resulting in a treatment break.

**Note:** Intensity modulated radiation therapy (IMRT) is permitted.

**Technical Factors:** Megavoltage equipment (minimum acceptable energy is 6 MV) with image guidance capable of delivering either 3D conformal radiation or static intensity modulation with a multileaf collimator or dynamic intensity modulation (using a multileaf collimator or tomotherapy) is required.

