### Follow-up for patients who are registered, but who never start study treatment

For all study participants who are registered to the trial but who never receive study intervention (regardless of eligibility), the follow-up requirements are specified below.

Randomized phase II and phase III: Baseline, off treatment, and post-treatment follow up (i.e., relapse, progression, and survival) data submission required. See the Data Submission Schedule accompanying the All Forms Packet.

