## 13.0 STATISTICAL CONSIDERATIONS

### 13.1 Study Endpoints

#### 13.1.1 Primary Endpoints:

- **Phase II:** The primary endpoint is cCR rate. The cCR rate is defined as the number of patients who achieved cCR at the end of TNT divided by number of patients included in the analysis population (see Section 13.4.1). This endpoint will be assessed within 8-12 weeks after completion of TNT. If there is a cCR, then the patient will be counted in the numerator. If there is a near-complete response (nCR) then a re-evaluation within 4-8 weeks will be performed. If the tumor has evolved to a cCR, then the patient will be counted in the numerator. Otherwise, the patient will be deemed as NOT achieving cCR status.
- **Phase III:** Disease-free survival (DFS): is defined as the time from date of randomization to the date of first occurrence of the following events:
  - Death due to all causes
  - Tumor that recurs locally after an R0 TME
  - Tumor that regrows after an initial apparent clinical and radiological CR and cannot be surgically removed with an R0 TME\*
  - M1 disease diagnosed at any point after the initiation of treatment

\* Regrowth for patients who are on watch and wait approach (regardless of treatment assignment) that can be surgically removed with an R0 TME will NOT be a DFS event

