## 13.4 Statistical Analysis Plan

### 13.4.1 Analysis Populations:

- **Intent-to-Treat (ITT) Population:** ITT population includes all patients who are properly randomized, regardless of the actual treatment received. The treatment grouping will be according to the original assignment at randomization.
- **Modified Intent-to-Treat (mITT) Population:** mITT population includes all patients who are properly randomized, completed LCRT and started at least one dose of protocol defined chemotherapy treatment. The treatment grouping will be according to the original assignment at randomization.
- **Per-Protocol (PP) Population:** PP population includes all patients who are deemed eligible after randomization, properly randomized, and received at least three cycles of chemotherapy after LCRT. The treatment grouping will be according to the actual treatment received during the first cycle of the chemotherapy.
- **Safety Population:** Safety population includes all patient who received any dose of treatment defined by protocol.

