**Phase III Portion:**

The Phase III hypothesis testing analyses will be performed on ITT population. Sensitivity analyses will be performed on mITT and PP population. At interim and final analyses, stratified Cox model will be conducted to compare DFS in the experimental arm to DFS in the control arm with stratification factors as stratum, based on all data collected at the analysis time point.

- **Interim Analysis Decision Rule:** The interim analysis will be conducted when 50% of targeted events (about 143) which is estimated around 4.5 to 4.9 years after the first patient is randomized (about 3.6 to 8.4 months after all patients are enrolled). If the observed HR (stratified by stratification factors) at interim analysis is  $> 1.00$ , we will conclude that the chance of DFS in experimental arm being superior to that in control arm is too low. The results will be presented to Alliance DSMB and NCI for potential public release.
- **Final Analysis Decision Rule:** The final DFS analysis will be performed when at least 285 DFS events are observed combining the two arms. Stratified Cox model will be conducted to compare DFS in the experimental arm A to DFS in the control arm B. If the one-sided p-value of the comparison is  $< 0.025$ , then we will conclude the DFS in the experimental arm is superior to the control arm.

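### Phase III DFS runs from randomization in the ITT population, but its distant-metastasis component opens only when treatment starts; a small mismatch that one line of wording removes

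*Combined protocol and SAP*

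**What the plan says.** Section 13.1.1 gives phase III DFS a clock that "is defined as the time from date of randomization to the date of first occurrence of the following events". There are four events. Death is unrestricted: "Death due to all causes". Local recurrence after an R0 TME, and regrowth that cannot be removed with an R0 TME, carry no condition about treatment start. The fourth does: "M1 disease diagnosed at any point after the initiation of treatment".

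On the population, section 13.4.2 says "The Phase III hypothesis testing analyses will be performed on ITT population", and section 13.4.1 says "ITT population includes all patients who are properly randomized, regardless of the actual treatment received". A patient who is randomized and never treated is therefore in the primary analysis.

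On timing, section 4.5.2 assigns the arm straight after registration ("After the patient has been registered into the study, the values of the stratification factors will be recorded", followed by the allocation), and section 7.1 says chemoradiation "should be initiated within 28 days following protocol registration".

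On data, section 12.5 requires the following for patients who are registered but never start: "Baseline, off treatment, and post-treatment follow up (i.e., relapse, progression, and survival) data submission required".

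**The concern.** The clock, the population and the event window should agree, and for metastasis they do not. The clock opens at randomization and the population is everyone randomized, but the window for metastasis opens only at treatment start. Two groups fall outside it:

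- patients whose metastases are found between randomization and the start of treatment;
- patients who never start treatment and so have no date at which the window opens.

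For both, the metastasis finding is not an event. The patient stays in the risk set until one of the other components occurs or follow-up ends.

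The second group matters more. No blinding is described and the arm is known before the first dose, so non-start could differ by arm. The arm with more never-starters would then lose more metastasis events and look better than it is. No other planned efficacy analysis would show this. The phase II analyses, the DFS sensitivity analyses and the secondary endpoints all use the mITT and PP populations (sections 13.4.2 and 13.4.3), and section 13.4.1 defines both so that never-starters are excluded.

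**Working it through.** **1. The plan's own figures (section 13.3.2).** Inputs: HR 0.70, one-sided alpha 0.025, 85% power, 1:1 allocation, 285 events, control 3-year DFS 76%, 760 patients at 180 per year, minimum follow-up 4 years.

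- Schoenfeld events: 4 × (1.960 + 1.036)² / (ln 0.70)² = 283.
- Power at 285 events: Φ(0.3567 × √(285/4) − 1.960) = 85.3%, or 85.1% allowing for the futility look.
- Probability of stopping at 143 events under the alternative: Φ(−0.3567 × √(143/4)) = 0.016, as stated.
- Expected events, with exponential DFS: 161.4 + 122.3 = about 284.

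The design figures reproduce.

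**2. Upper bound on gap events.** The control hazard is −ln(0.76)/3 = 0.0915 per year, the experimental hazard is 0.70 times that, and the gap is 28/365.25 = 0.0767 years. Assume that every patient waits the full 28 days and that every early event is a metastasis.

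- Control: 380 × (1 − exp(−0.0915 × 0.0767)) = 2.66.
- Experimental: 1.86 by the same formula.
- Total: 4.5, or 5.3 with the control hazard in both arms.

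That is at most about 5 of 285. The section 5.0 calendar schedules no restaging CT or MRI between the pre-study work-up and weeks 32-38, so detection in the gap would be incidental.

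**3. Metastasis events among never-starters.** The documents give neither a never-start rate nor the share of first DFS events that are metastases. Assume 1% to 5% and 50% to 80%. The expected event fraction is 283.65/760 = 0.373.

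- Low: 760 × 0.01 × 0.373 × 0.50 = 1.4.
- High: 760 × 0.05 × 0.373 × 0.80 = 11.3.

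These are counts before adding back patients who later die or recur locally and so become events.

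**4. Bias under the null.** Let e and c be the never-start fractions in the experimental and control arms, and m the metastasis share. If every uncounted metastasis is lost for good (the worst case), the apparent HR is about (1 − e·m)/(1 − c·m). The one-sided error is then 1 − Φ(1.960 + ln(HR) × √(285/4)).

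| e vs c (assumed) | HR, m = 0.50 | HR, m = 0.80 | One-sided alpha |
|---|---|---|---|
| 2% vs 2% | 1.000 | 1.000 | 0.025 |
| 3% vs 1% | 0.990 | 0.984 | 0.030 to 0.034 |
| 5% vs 2% | 0.985 | 0.976 | 0.034 to 0.040 |
| 5% vs 1% | 0.980 | 0.968 | 0.037 to 0.046 |

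If half of the uncounted patients later die and count (an assumption), m is in effect halved. For 5% vs 2% the HR becomes (1 − 0.025m)/(1 − 0.01m) = 0.993 at m = 0.50 and 0.988 at m = 0.80, so about 0.99.

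**5. Power.** If 5, 10 or 15 events were lost and not replaced, power would be 84.7%, 84.1% or 83.4%. Section 13.4.2 waits for at least 285 events, so the main result is delay.

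**The case against.** **The word treatment is not qualified.** Sections 7.0 and 7.1 refer to protocol treatment and section 12.5 to study treatment, but the metastasis bullet says only treatment. A patient who declines protocol therapy and is treated elsewhere has arguably initiated treatment, and a later metastasis would count. That reading is open, and it would shrink the never-starter group. It does not help a patient whose metastases are found before any treatment, and it leaves a primary-endpoint event to case-by-case judgment in a trial where the arm is known.

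**Both arms begin with the same chemoradiation.** A patient unwilling to take the triplet can start chemoradiation and decline at consolidation; treatment has then begun and metastases count. This stands. It weakens the case for differential non-start and makes gap losses roughly equal between arms.

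**The 5% allowance in section 13.2 is not a never-start rate.** It covers cancellations and major violations for phase II evaluability. This stands too, and 5% serves here only as an upper assumption.

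**The contrast with time to distant metastasis is limited.** Section 13.1.2 defines that endpoint from randomization with no treatment-start condition, so the two definitions do differ. Its analysis is on mITT and PP, however, so a never-starter's metastasis is not analysed there either.

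**Stronger readings that a reader might infer.** One is that these patients can never have a DFS event, or only by dying. The other components in section 13.1.1 are unconditional: local recurrence after an R0 TME counts as well as death. Another is that the phase III test is not an ITT analysis. All properly randomized patients are analysed as assigned; the fault is in one component of the endpoint. A third is that the comparison is biased toward the triplet. No passage gives an arm-specific non-start rate, and the direction is unknown.

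**Conclusion.** The mismatch is real on the text, and no other section removes it. Followed as written, the definition leaves some randomized patients' metastases out of the primary endpoint although section 12.5 requires their relapse and progression data. The patient's event is then delayed, or lost if follow-up ends without one.

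The size is probably small. The gap bound of about 5 events rests on every patient waiting the full 28 days and every early event being a metastasis. The range of about 1 to 11 among never-starters, and the null HR of about 0.97 to 0.985 for an assumed 5% against 1% to 2%, rest on rates that the documents do not give; the HR range also ignores later deaths that would count. With equal non-start there is no bias under the null. The event target and stated power are sound.

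This is a minor point, worth settling because it concerns the phase III primary endpoint and costs almost nothing. It does not invalidate the design.

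**What to change.** Reword the fourth DFS event in section 13.1.1 to: *M1 disease diagnosed at any time after randomization, whether or not protocol treatment was started*, with the event dated at diagnosis. The window then matches the DFS clock and the ITT population, and the doubt about what counts as treatment goes.

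The cost is one line of wording, best made before the 143-event interim analysis, whose futility rule depends on the observed HR. Section 12.5 already requires relapse and progression data on never-starters, so nothing new is collected. The 760 patients, 285 events and one-sided alpha of 0.025 stay as they are; a few events may be added or dated earlier.

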### 13.1.2 Secondary Endpoints:

- Organ-preservation-time (OPT): is defined as time from the date of randomization to the date of the first occurrence of the following events:
  - TME performed or attempted
  - Tumor that regrows after an initial apparent clinical and radiological CR
  - Death due to all causes
- Time to distant metastasis (TDM): is defined as time from the date of randomization to the date of first documented distant metastasis.
- Overall survival (OS): The OS is defined as time from the date of randomization to the date of death due to all causes.
- Adverse Events (AE) Rate: is defined as the proportion of patients experienced at least one Grade 3, Grade 4, or Grade 5 of each type of AE.

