|----------------------|----------------------------------------------------------------|
| 5-Fluorouracil       | 2400 mg/m  continuous iv infusion over 46-48 hours |
| Leucovorin           | 400 mg/m  iv day 1                                 |
| Irinotecan           | 150 mg/m  iv day 1                                 |
| Oxaliplatin          | 85 mg/m  iv day 1                                  |
| Repeat every 2 weeks |                                                                |

In the PRODIGE23 trial (that used doses as detailed above except for a slightly higher dose of irinotecan at 180 mg/m^2 iv day 1), although slightly higher rates of  $\geq$  grade 3 neutropenia (2.8% vs 0) and capecitabine discontinuation (8% vs 3%;  $p < 0.02$ ) were noted during LCRT in the TNT arm, they did not impact proportion of patients undergoing subsequent surgery (92.2% vs 94.8%;  $p = 0.26$ ) perioperative morbidity or quality of life. In fact, trends towards improvement in non-therapeutic surgery (0% vs 3.7%); metastatic disease at pre-surgical staging (1% vs 4.7%) and better tolerance of subsequent adjuvant therapy ( $\geq$  grade 3 toxicities 11.7% vs 20.7%) were noted favoring the TNT arm. Importantly, the 7-year updated data from PRODIGE23 presented at ASCO 2023 demonstrated significantly better DFS, metastasis-free survival and overall survival in the TNT-arm versus the standard of care arm (68% vs. 63% DFS)[44]. These data support the use of a triplet TNT approach to improve DFS outcome for rectal cancer patients.

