### 7.3 Surgery

All patients will undergo assessment at 8-12 weeks post-TNT completion. If patients have a cCR (no tumor on endoscopy, MRI, or clinical exam using the MSK regression schema) then patients may be offered a WW approach or TME depending on the outcome of a thorough discussion with their treating physician concerning the risks and benefits of each approach and both they and their physician agree with the intended approach. If the patients have an incomplete response (any evidence of residual tumor by endoscopy, MRI or clinical exam using the MSK regression schema) then they be recommended to undergo TME (not mandated and identical to OPRA). Of note, and as in OPRA, if patients have a near complete response (nCR) then patients can undergo a repeat assessment 8 weeks later (+/-2 weeks). If there is any evidence that the tumor has stopped responding, persists or regrows then the patient will be recommended to undergo TME (e.g. nCR that fails to evolve to a cCR at 20 weeks (+/- 4 weeks) post-completion of TNT OR local regrowth after initial cCR determination). If there is a discrepancy between MRI and endoscopy/DRE then endoscopy/DRE should take precedence in the decision making on whether to proceed to WW or TME.

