### 12.2 Criteria for Discontinuation of Protocol Treatment/Intervention

In the absence of treatment delays due to adverse event(s), treatment may continue until one of the following criteria applies:

- Disease progression during neoadjuvant treatment which precludes surgery (e.g., tumor perforation that prohibits completion of treatment or treatment as designated per Arm or detection of distant metastases)
- Intercurrent illness that prevents further administration of treatment
- Unacceptable adverse event(s)
- Patient decides to withdraw from the study
- General or specific changes in the patient's condition render the patient unacceptable for further treatment in the judgment of the investigator
- Clinical progression
- Patient non-compliance
- Pregnancy (if applicable)
  - All women of child bearing potential should be instructed to contact the investigator immediately if they suspect they might be pregnant (e.g., missed or late menstrual period) at any time during study participation.
  - The investigator must immediately notify CTEP in the event of a confirmed pregnancy in a patient participating in the study.
- Termination of the study by sponsor

The reason(s) for protocol therapy discontinuation, the reason(s) for study removal, and the corresponding dates must be documented in the Case Report Form (CRF).

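### Organ-preservation-time has no failure event for patients who never reach cCR and never have TME, so an uncleared tumor counts as a preserved organ

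*Combined protocol and SAP*

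**What the plan says.** Section 13.1.2 measures OPT from randomization to the first of three events: "TME performed or attempted"; "Tumor that regrows after an initial apparent clinical and radiological CR"; and "Death due to all causes". No other event is listed.

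Two other sections describe patients who may keep their tumor and never have surgery:

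- Section 7.3 says that patients with an incomplete response are "recommended to undergo TME (not mandated and identical to OPRA". A near-complete response (nCR) that does not become a cCR also leads only to a recommendation.
- Section 12.2 lists, as a reason to stop protocol treatment, "Disease progression during neoadjuvant treatment which precludes surgery", and includes detection of distant metastases. Section 12.1 also names local or regional progression that precludes surgery.

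DFS in Section 13.1.1 counts "M1 disease diagnosed at any point after the initiation of treatment". OPT has no such event.

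Section 13.4.3 analyzes secondary endpoints in the mITT and PP populations by Kaplan-Meier and stratified Cox regression. It gives no censoring or competing-risk rule for OPT. OPT is the first secondary objective (2.2.1), and Section 1.2 announces a comparison of 3-year organ preservation rates.

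**The concern.** The regrowth event requires an earlier complete response, so it cannot happen to a patient who never had one. If that patient also never goes to TME, OPT continues until death or last follow-up, and the Kaplan-Meier curve carries the patient as organ-preserved. These are among the poorest results of treatment: persistent tumor with surgery declined, or progression or metastasis that closed the surgical option.

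A patient who did clear the tumor, then regrew and declined TME, fails at regrowth. The rule therefore ranks a tumor that never cleared above one that cleared and came back. The reported organ preservation rate would include patients whom few readers would regard as organ preservation successes, in an endpoint tied to a central aim of the trial.

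**Working it through.** The plan states no power, event count or expected rate for OPT, so there is no figure to reproduce. The check has three parts.

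**1. Patient paths against the three events**

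- cCR, then regrowth, TME done, refused or impossible: event at regrowth.
- No cCR, TME performed or attempted: event at TME.
- Incomplete response, TME declined, tumor in place: no event before death or censoring.
- nCR that never becomes cCR, TME declined: no event before death or censoring.
- Metastasis or surgery-precluding progression before any cCR, no TME: no event before death or censoring.

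The last three paths are the gap.

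**2. Does another rule close it?**

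- M1 disease is captured by DFS (13.1.1) and by time to distant metastasis (13.1.2), but neither feeds into OPT.
- The mITT population (13.4.1) keeps anyone who completed LCRT and started consolidation chemotherapy. PP keeps eligible patients with at least three cycles. Early dropouts leave these sets, but most patients on the three paths would stay.
- Section 13.4.3 has no OPT-specific censoring.

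No other section counts persistent tumor, declined TME or unresectable progression as an OPT failure.

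**3. Illustrative size**

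Inputs from the documents: at most 380 patients per arm (13.2); cCR of 50% in control and 67% in experimental (13.3.1), so 50% and 33% without cCR.

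Assumed input: r, the share of non-cCR patients who never have TME. The documents do not give it. I use 5-8%, an order of magnitude suggested by the PRODIGE23 surgery rates in Section 1.1 ("they did not impact proportion of patients undergoing subsequent surgery (92.2% vs 94.8"): 100 - 92.2 = 7.8% and 100 - 94.8 = 5.2% without surgery. Surgery was part of the plan in both arms of that trial, so this is a guide only.

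Patients affected = 380 x (1 - cCR) x r:

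- Control: 380 x 0.50 x 0.05 = 9.5; at 8%, 15.2.
- Experimental: 380 x 0.33 x 0.05 = 6.3; at 8%, 10.0.
- Both arms: about 16 to 25.

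Points added to apparent organ preservation, ignoring deaths and censoring = 100 x (1 - cCR) x r:

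- Control: 50 x 0.05 = 2.5; 50 x 0.08 = 4.0.
- Experimental: 33 x 0.05 = 1.65; 33 x 0.08 = 2.64.

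Shift in the arm difference (experimental minus control) = 33 x r(exp) - 50 x r(control):

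- r equal at 5%: 1.65 - 2.5 = -0.85 points. r equal at 8%: 2.64 - 4.0 = -1.36.
- r of 5% in control and 20% in experimental: 6.6 - 2.5 = +4.1.
- r of 20% in control and 5% in experimental: 1.65 - 10.0 = -8.35.

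The sign depends on r in each arm, which is unknown.

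**The case against.** The best defense is that OPT is meant as TME-free survival. Section 1.4 uses organ preservation and TME-free survival almost interchangeably when it describes OPRA. On that reading an unoperated patient is event-free by design, and metastasis is left to DFS and time to distant metastasis. The regrowth bullet defeats this: a pure TME-free endpoint would not count regrowth without surgery, and OPT does. The list fits neither TME-free survival nor tumor-free organ preservation.

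Three stronger readings are tempting, and the documents do not support them.

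- A reader might infer that the gap always works against the better regimen. In the PRODIGE23 figures the arm with better DFS had more patients without surgery (7.8% against 5.2%), while metastases at pre-surgical staging were fewer (1% against 4.7%). These point in opposite directions, and the arithmetic above gives either sign.
- A reader might apply 5-8% to all 760 patients and get 38-61. Only patients without cCR can fall into the gap, and the design assumes these to be 33-50% of each arm.
- A reader might add the inflation to OPRA's 53% and expect 56-61%. OPRA's exact event definition is not in the documents. If OPRA left unoperated patients event-free, 53% already contains them.

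Other limits stand. M1 disease does not always exclude TME, since Section 11.3.1 contemplates pelvic resection with distant tumor present. The OPRA watch-and-wait patients in Section 13.5.1 who declined further treatment (four) or could not have TME because of progression (three) show that both happen. They do not size the gap, because those with an earlier complete response would already have an OPT event at regrowth.

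**Conclusion.** Wrong as written, for a secondary endpoint. Followed literally, OPT scores a tumor that never cleared as organ-preserved until death or censoring, and one that cleared and returned as a failure. This follows from the event list in Section 13.1.2 together with Sections 7.3 and 12.2, and rests on no numerical assumption.

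The size does rest on an assumption. If 5-8% of non-cCR patients never have TME, with the design cCR rates and 380 per arm, about 16-25 patients are affected: 2.5-4.0 points in control and 1.7-2.6 in experimental, before deaths. The mITT and PP populations will be somewhat smaller than 380 per arm. Organ preservation is overstated in each arm, but no direction can be given for the comparison between arms. The cCR and DFS analyses and the monitoring rules in Section 13.5.1 do not use OPT and are unaffected.

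**What to change.** Change the endpoint coding only; this has no bearing on who should have surgery. Add two events to OPT in Section 13.1.2:

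1. cCR not achieved at the final response assessment defined in Section 13.1.1, dated at that assessment. This is the first post-TNT assessment for an incomplete response and the re-evaluation for an nCR.
2. M1 disease, or progression that precludes surgery in the sense of Section 12.2, before any cCR, dated when documented.

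Apply both to every patient whether or not TME follows, so that the event does not depend on later treatment. Report the present definition, or TME-free survival, as a supplementary analysis.

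Two details need settling so that the dates are unambiguous. The nCR re-evaluation is within 4-8 weeks in Section 13.1.1 but 8 weeks (+/- 2) in Section 7.3, and these must be reconciled. For patients who stop pre-operative treatment early, Section 12.3.1 leaves assessments to the treating team, so a rule for a missing final assessment should be stated with the OPT censoring rules.

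The cost is small. Section 6.1.4 already requires end-of-TNT and progression reports, and Section 12.2 requires discontinuation reasons and dates. The organ preservation rate becomes slightly less favorable, some events move a few weeks ahead of TME, and a rare patient who clears the tumor after the final assessment counts as a failure. The supplementary analysis keeps that last group visible.

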### **2.2 Secondary objective(s)**

**2.2.1** To evaluate and compare organ-preservation-time (OPT) between two treatment arms.

**2.2.2** To evaluate and compare time to distant metastasis between two treatment arms.

**2.2.3** To evaluate and compare overall survival (OS) between two treatment arms.

**2.2.4** To evaluate and compare toxicity profiles of TNT between two treatment arms.

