## 9.2 CTCAE Routine Reporting Requirements

In addition to the solicited adverse events listed in Section 9.1, the following table outlines the combinations of time points, grades and attributions of AEs that require routine reporting to the Alliance Statistics and Data Center. Questions about routine reporting should be directed to the Data Manager.

Combinations of CTCAE Grade & Attribution Required for Routine AE Data Submission on Case Report Forms (CRFs)

| Attribution | Grade 1 | Grade 2 | Grade 3 | Grade 4 | Grade 5 |
|-------------|---------|---------|---------|---------|---------|
| Unrelated   |         |         | a       | a       | a       |
| Unlikely    |         |         | a       | a       | a       |
| Possible    |         | a       | a, b    | a, b    | a, b    |
| Probable    |         | a       | a, b    | a, b    | a, b    |
| Definite    |         | a       | a, b    | a, b    | a, b    |

- a) **Adverse Events CRF** - Applies to AEs occurring between registration and within 30 days of the patient's last treatment date.
- b) **Adverse Events: Late CRF** - Applies to AEs occurring greater than 30 days after the patient's last treatment date, or as part of the Clinical Follow-up Phase or Survival Follow-up Phase.

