**13.4.3 Secondary Endpoints:**

The analyses of secondary endpoints will be conducted on mITT and PP population whenever it is applicable and plausible. Safety-related analyses will be performed on the safety population.

The distributions of time-to-event endpoints will be estimated, in each arm, using the method of Kaplan-Meier and compared by a stratified Cox regression model. The binary endpoints will be estimated, in each arm, and compared by chi-squared test or Fisher's exact test. Dose intensity and number of cycles will be summarized by mean, standard deviation, median, Q1, Q3, and range, in each arm, and compared by Wilcoxon Rank Sum test. The maximum grade for each type of adverse events that are possibly, probably, or definitely related to study treatments will be recorded for each patient. The frequency tables will be reviewed to determine the patterns. The overall adverse event rates for grade 3 or higher adverse events will be compared between two treatment groups using Chi-square test (or Fisher's exact test if the data in the contingency table is sparse).

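### The AE rate endpoint has no attribution limit, but the only AE-specific per-type tabulation is restricted to treatment-related events, and neither the attribution rule for the compared rate nor its time window is stated

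*Combined protocol and SAP*

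**What the plan says.** Secondary objective 2.2.4 is "To evaluate and compare toxicity profiles of TNT between two treatment arms". Section 13.1.2 turns this into an endpoint, the AE rate, which "is defined as the proportion of patients experienced at least one Grade 3, Grade 4, or Grade 5 of each type of AE". The unit is the AE type, the threshold is grade 3, and attribution is not mentioned.

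Section 13.4.3 has three AE-specific statements, in this order:

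- On recording: "The maximum grade for each type of adverse events that are possibly, probably, or definitely related to study treatments will be recorded for each patient".
- On use of that record: tables of how often each grade occurs are to be looked over for patterns.
- On comparison of the arms: "The overall adverse event rates for grade 3 or higher adverse events will be compared between two treatment groups using Chi-square test", with Fisher's exact test as the fallback for sparse tables.

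Earlier in 13.4.3 a general sentence says that binary endpoints will be estimated in each arm and compared by chi-squared or Fisher's exact test. On the population, "Safety-related analyses will be performed on the safety population".

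Section 9.2 governs collection. For the main AE form, which "Applies to AEs occurring between registration and within 30 days of the patient's last treatment date", grade 3-5 events are required in all five attribution rows, including unrelated and unlikely. For the late form, used after 30 days, they are required only in the possible, probable and definite rows. Section 9.0 has the investigator assign attribution.

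**The concern.** The endpoint and its AE-specific tabulation do not count the same patients. Someone whose only grade 3 or higher event of a given type is rated unrelated or unlikely meets the definition in 13.1.2 but is missing from the per-type tables in 13.4.3.

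Attribution is assigned by investigators who know the arm. No blinding is described, and under 7.2 the investigator chooses the control regimen. An investigator who expects irinotecan toxicity may call an event related in the triplet arm and unrelated in the doublet arm. A related-only toxicity profile is open to that kind of arm-dependent rating; a profile that ignores attribution is not.

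The trial tests the addition of a third drug, so the toxicity difference is what any gain in cCR or DFS will be weighed against. If the rule is left open, the compared rate can be computed in more than one way, and the choice could be made after the data have been seen.

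**Working it through.** The point is mainly definitional, and the plan states no figure to reproduce: it gives no expected AE rate and no power for this endpoint. The check sets the texts side by side.

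| | 13.1.2 endpoint | 13.4.3 tabulation | 13.4.3 overall comparison |
|---|---|---|---|
| Unit | each AE type | each AE type | overall rate |
| Grade | 3-5 | maximum grade | 3 or higher |
| Attribution | none stated | related only | none stated |
| Time window | none stated | none stated | none stated |
| Use | definition | reviewed for patterns | chi-square or Fisher's exact test |

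1. **Attribution.** The tabulation is narrower than the endpoint. The tested sentence carries no filter of its own, but it directly follows the related-only recording and its tables. An analyst could carry the filter over or leave it out.

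2. **How the plan words attribution elsewhere.** The grade 4 or higher monitoring rule in 13.5.1 states its relatedness condition in full. Silence in 13.1.2 is therefore most naturally read as no restriction. That is an inference, since 13.1.2 does not say so.

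3. **Unit.** The endpoint is per type, while the AE-specific test is on an overall rate.

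4. **Window.** Under 9.2, a rate that ignores attribution is complete for grade 3-5 events up to 30 days after last treatment. After that only related events are required. A rate taken over both periods would be unrestricted early and related-only late.

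**Illustrative size.** Two inputs are assumed because the documents give neither: a grade 3+ rate regardless of attribution of r = 40%, and a share u = 10-20% of those patients who have only unrelated events.

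- Gap between the two definitions within one arm = r × u = 0.40 × 0.10 to 0.40 × 0.20 = 4 to 8 points.
- With the same r and u in both arms, this gap cancels in the arm difference.
- With the same r but different shares, the arm difference moves by r × (difference in u). For a difference in u of 0 to 10 percentage points, that is 0 to 0.40 × 0.10 = 0 to 4 points.
- For scale, taking 380 per arm from 13.2 as the size of the safety population, the SE of one arm's rate is √(0.40 × 0.60 / 380) = 2.5 points. The SE of the difference is √2 × 2.5 ≈ 3.6 points, so a 4-point shift is 4 / 3.6 ≈ 1.1 SE.

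**The case against.** A reader might infer that the plan's toxicity comparison as a whole rests on unblinded attribution. The documents do not support that. The related-only tables are described as reviewed for patterns, with no test attached, and the sentence that names the AE test has no relatedness limit. This stands, and it limits the point to an inconsistency and an ambiguity.

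The general binary-endpoint sentence in 13.4.3 may also cover the endpoint as defined. Of the four secondary endpoints in 13.1.2, three are times to event and the AE rate is the only binary one. On that reading the per-type rate without an attribution limit is already to be estimated and compared, and the related-only table is an addition. The reading is plausible, but 13.4.3 does not make the link, and its only AE-specific per-type rule is still restricted to related events.

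A reader might further infer that 13.1.2 specifies an all-cause rate, or that early and late events will be pooled. Neither is stated. Section 13.1.2 is silent on attribution. Section 9.2 puts the two periods on separate forms, so they can be kept apart, and an objective about TNT toxicity points to the treatment period. What remains is that no window is written down.

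Finally, the endpoint carries no stated power or decision threshold, and the monitoring rules in 13.5.1 are defined separately from it. That limits the consequences but does not remove the mismatch on a stated secondary objective.

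**Conclusion.** The point holds in a limited form. The endpoint in 13.1.2 has no attribution limit, while the only AE-specific per-type tabulation leaves out events rated unrelated or unlikely, on ratings made without any described blinding. Whether the overall grade 3+ comparison is filtered is not settled by the text, and no time window is given for either.

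The definitional mismatch follows from the text alone and depends on no assumed number. Its size does not: the 4-8 point gap within an arm needs the assumed 40% rate and 10-20% share, and it should not be quoted as an effect on the arm difference. An effect there requires the unrelated share to differ between arms. Even an assumed 10-point gap gives about 4 points, or 1.1 SE, and only if the compared rate is filtered.

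This is a worthwhile and cheap clarification of a secondary safety analysis. It does not affect either primary analysis.

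**What to change.** In 13.4.3, state that grade 3-5 AEs will be tabulated and compared between arms regardless of attribution, by type and overall, in the safety population, from start of protocol treatment to 30 days after last treatment. Add the same attribution rule and window to the definition in 13.1.2. Present treatment-related AEs as a supportive table, and late related AEs (more than 30 days after last treatment) separately.

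No new data are needed, because 9.2 already requires grade 3-5 events of every attribution within that window. The cost is a wording change and one extra table. The downside is that reported AE rates will be somewhat higher than related-only rates.
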